### Variables measurement

2.10

At the baseline stage, sociodemographic variables will be collected. Physical examinations and questionnaires are scheduled to be completed at the baseline, upon discharge, and at the end of the intervention (**Table 1**).

Sociodemographic Variables: A custom-designed demographic questionnaire will be utilized to measure the following variables: the child’s gender and age, the ages of the parents, marital status, type of household registration, number of persons in the household, education level, occupation, income status, as well as the child’s asthma symptoms and a detailed medical history.Anthropometric Variables: Each participant’s height, weight, waist circumference, and blood pressure will be measured twice, using certified instruments to ensure accuracy. Height and weight measurements will be carried out using fully calibrated, certified electronic devices. The BMI will be calculated by dividing the weight in kilograms by the square of the height in meters. To measure the waist circumference, a measuring tape will be used at the level of the navel.Pulmonary Function Tests: The MasterScreen series pulmonary function testing system from Jaeger (Germany) will be used to conduct pulmonary function tests. Key indicators include the Forced Expiratory Volume in 1 second (FEV_1_), Forced Vital Capacity (FVC), the FEV_1_/FVC ratio, Peak Expiratory Flow (PEF), and the forced expiratory flow at 25%, 50%, and 75% of FVC exhaled (FEF_25_%, FEF_50_%, FEF_75_%) (30).

**Table 1 T1:** The schedule of enrolment, interventions, and assessments.

Study period	Recruitment	Intervention	
Timepoint	0	Discharge	3 Months
Eligibility screen	✓		
Informed consent	✓		
Allocation	✓		
Sociodemographic variables	✓		
C-ACT	✓	✓	✓
PFT	✓	✓	✓
s-EMBU-C	✓	✓	✓
PHQ4	✓	✓	✓
PSSS-SF	✓	✓	✓
NGSES-SF	✓	✓	✓
EQ-5D-5L	✓		✓
Smoking	✓		✓
Alcohol consumption	✓		✓
B-PSQI	✓		✓
FCS-SF	✓		
eHEALS	✓		

B-PSQI, The new Brief Version of the Pittsburgh Sleep Quality Index-Short Form; C-ACT, Childhood Asthma Control Test; eHEALS, The eHealth Literacy Scale; FCS-SF, The Family Communication Scale-Short Form; EQ-5D-5L, EuroQol-5 Dimensions 5 Levels; PFT, Pulmonary Function Tests; PHQ-4, the abbreviated Patient Health Questionnaire-4; PSSS-SF, The Perceived Social Support Scale; NGSES-SF, The New General Self-Efficacy Scale-Short Form; s-EMBU-C, Short-Form Egna Minnen av Barndoms Uppfostran for Chinese.

Post-discharge sustained engagement will be maintained through WeChat, telephone, or SMS communication to ensure participants remain fully informed and actively involved. During these interactions, participants will receive timely updates on research progress, resolution of any emerging concerns, and prompt reminders for upcoming follow-up assessments.

Standardized data entry for this study will be performed using an electronic data capture (EDC) system. First, double data entry by two independent operators will ensure accuracy, followed by logical validation checks on all raw data. Sensitive information will be encrypted using the Unicode encoding scheme. Data will be stored on password-protected servers with role-based access control (only authorized researchers may access de-identified data), and a real-time backup system will be deployed to off-site cloud storage to ensure data integrity and disaster recovery capabilities.

After collecting the relevant data of the participants, we will immediately take measures to delete all personally identifiable information, so as to protect the confidentiality of the data. This process involves replacing personally identifiable information with a unique code. Only a few authorized research team members can access the key connecting these codes with the actual identification information. The key will be stored in a separate and highly secure place. Without the explicit and informed consent of the participants, we will not share any personal information with third parties under any circumstances. All members of the research team are obliged to sign a confidentiality agreement. These agreements are designed to ensure that each team member complies with the highest standards of privacy. From the beginning to the end or even after the end of the study, all personal information will be securely stored on a dedicated server. Only authorized researchers can access the server.

### Questionnaires

2.11

Childhood Asthma Control Test (C-ACT): The C-ACT is an important tool for measuring how well asthma symptoms are controlled in children. It has two parts with a total of seven questions in Chinese version. The first part has four questions for the child to answer. Each question is scored from 0 to 3, based on how the child feels about their asthma control. The second part has three questions for the parent to answer. Each question is scored from 0 to 5, based on how often the child has asthma symptoms in the last four weeks. The total score of the C-ACT goes from 0 to 27. A score of 23 or higher means asthma is fully controlled, with few symptoms affecting daily life. A score between 20 and 22 means partial control, where symptoms are somewhat managed, but some problems remain. A score of 19 or less means asthma is not controlled, and stronger treatments may be needed (31).Short-Form Egna Minnen av Barndoms Uppfostran for Chinese (s-EMBU-C): The s-EMBU-C is a questionnaire designed to evaluate how children see their parents’ parenting styles. The child fills out this questionnaire. There are separate versions for fathers and mothers. Each version has 21 questions, divided into three parts: rejection (6 items), emotional warmth (7 items), and overprotection (8 items). The questions are scored using a scale from 1 to 4. “Never” gets 1 point, “Occasionally” gets 2 points, “Frequently” gets 3 points, and “Always” gets 4 points. Item 15 is scored in reverse. The scores for each part are found by adding up the points for each question in that part. A higher score in a part means the parent shows that parenting style more often. The total score for both versions can range from 28 to 112 points (32).The assessment of depression and anxiety will use the Chinese version of the Patient Health Questionnaire-4 (PHQ-4). This is a short self-report tool to check depression and anxiety symptoms over the past two weeks. The PHQ-4 has four questions. The first two questions focus on depression symptoms, and the last two focus on anxiety symptoms. Each question is rated on a scale from 0 to 3: “Not at all” (0 points), “Several days” (1 point), “More than half the days” (2 points), and “Nearly every day” (3 points). The total score goes from 0 to 12. In studies in China, the PHQ-4 has shown high validity and reliability, with a Cronbach’s alpha of 0.833 (33).The Chinese version of the Perceived Social Support Scale-Short Form (PSSS-SF) is used to measure the level of social support a person feels they receive. The scale has three questions, each about a different type of support: family support (Item 1), friend support (Item 2), and other support (Item 3). Each question is scored on a 7-point scale from 1 (Strongly Disagree) to 7 (Strongly Agree). The total score can range from 3 to 21. Higher scores mean more social support, showing that the person’s social network provides more help, both emotionally and practically (34).The Chinese version of the New General Self-Efficacy Scale (NGSES-SF) is used to measure a person’s confidence in their ability to succeed in tasks or face challenges. It has three questions, each focusing on a different aspect of self-efficacy. Item 1 looks at how capable a person feels in handling a situation. Item 2 focuses on how confident a person is in their skills. Item 3 looks at how confidence in one area can apply to other areas. The NGSES-SF uses a 5-point Likert scale. Respondents can choose from 1 (Strongly Disagree), showing low confidence, to 5 (Strongly Agree), showing high confidence. The total score can range from 3 to 15 (35).The Chinese version of the EQ-5D-5L scale (EuroQol-5 Dimensions 5 Levels) will be used to measure quality of life. The scale looks at five important health areas: mobility, self-care, usual activities, pain/discomfort, and anxiety/depression. For each area, there are five levels, ranging from “no problems” to “extreme problems.” This lets respondents choose the level that best matches their condition. It gives a complete view of a person’s health in these five areas. The EQ-5D-5L also includes a Visual Analogue Scale (VAS). This part lets participants rate how they feel about their current health on a scale from 0 to 100. A score closer to 0 means worse health, while a score closer to 100 shows better health (36).Smoking behavior will be assessed using a self-designed questionnaire. The questionnaire has four multiple-choice questions to categorize smoking habits. These questions are meant to find out: whether the person smokes, how long it has been since they quit smoking (if they quit), how many cigarettes they smoke daily, and when they started smoking. The first question is “Do you have a smoking habit?” with these options: (1) Yes, I smoke regular cigarettes; (2) Yes, I smoke e-cigarettes; (3) I smoke both; (4) I used to smoke (now quit); (5) I have never smoked. Based on their answers, participants will be grouped into two categories: smokers, which include people who currently smoke regular cigarettes, e-cigarettes, or both; and non-smokers, which include those who have never smoked and those who have quit smoking (37).Alcohol consumption will be evaluated using a self-developed 7-item multiple-choice questionnaire designed to assess: 1) current/historical alcohol use status, 2) age of drinking initiation, 3) age of drinking cessation (if applicable), 4) preferred alcoholic beverage types, 5) average daily alcohol intake, 6) pre-quitting daily consumption volume, and 7) perceived anxiety related to alcohol cessation. The instrument begins with the core screening question: ‘Which best describes your alcohol consumption pattern?’ Respondents choose from four mutually exclusive categories: (1) Never consumed alcohol; (2) Current regular drinker; (3) Former drinker who has quit; (4) New-onset drinker in the past year (43, 44).The Chinese version of the Pittsburgh Sleep Quality Index Short Form (PSQI-SF) is a shorter version of the Pittsburgh Sleep Quality Index, made to measure sleep quality. The scale has six items, covering five key aspects of sleep. Items 1 and 2 measure sleep efficiency. Item 3 measures how long it takes to fall asleep. Item 4 looks at sleep duration. Item 5 checks for sleep disturbances. Item 6 looks at overall sleep quality. The total score on the PSQI-SF goes from 0 to 15. A higher score means worse sleep quality (38).The Chinese version of the Family Communication Scale Short Form (FCS-SF) is made to measure how well family members communicate. The scale has four items that assess family communication. It uses a 5-point Likert scale, where 1 means “strongly disagree” and 5 means “strongly agree.” The total score goes from 4 to 20. A higher score means better communication among family members (39).The Chinese version of the Electronic Health Literacy Scale (eHEALS) measures how well parents of children can search for, evaluate, and use electronic health information to solve health problems. The scale has five items in one dimension. It uses a 5-point Likert scale, where 1 means “strongly disagree” and 5 means “strongly agree.” The total score ranges from 5 to 25. A higher score means better electronic health literacy (40).

### Statistical analysis

2.12

This study will collect quantitative data through questionnaires and process the data using Microsoft Excel. Data analysis will follow the intention-to-treat principle. For continuous variables, descriptive statistics will show means ± standard deviations or medians and interquartile ranges (P25, P75), depending on the data. Normally distributed continuous variables will be compared using the Student’s t-test or one-way analysis of variance (ANOVA). Non-normally distributed data will be analyzed with non-parametric tests. The normality of the data will be checked using the Kolmogorov-Smirnov test. Categorical variables will be shown as sample percentages (n) and analyzed using the Chi-square test. For missing data, multiple imputation using chained equations (MICE) will be used, with 50 iterations to ensure convergence. The imputation method will be predictive mean matching (PMM), with 5 neighbors and 20 imputed datasets.

In the cross-sectional data analysis, this study will use linear regression, logistic regression, and structural equation modeling (SEM) to examine the relationships between behavioral patterns and mobile health applications. Given the nested structure of parent-child dyads within families, we employed multilevel models with family-level random intercepts to account for within-family correlations. For child health outcomes (asthma-related events and symptoms), a two-level negative binomial model was utilized to estimate IRRs and 95% CIs, adjusting for family-level variables (parents’ parenting styles, household income, marital status) and child-level variables (age, sex). For parental outcomes (continuous data), a two-level linear mixed model was applied to evaluate intervention effects, adjusting for family-level variables (marital status, household income) and parent-level variables (age, education, parents’ parenting styles). *Post hoc* comparisons of estimated marginal means were conducted using the emmeans package to test between-group differences. Model fit was validated through convergence checks, residual analysis, and overdispersion testing for count data. All analyses were performed in R (version 4.3.1; R Foundation for Statistical Computing, Vienna, Austria) using the lme4 package (version 1.1-33). An independent statistician with no conflicts of interest conducted the analysis. All statistical tests were two-tailed, with a significance level of 0.05.

After the intervention, we will conduct structured interviews with participants to evaluate the attractiveness, acceptability, usability, and overall satisfaction with the AI-HEALS-based intervention model. Participants will be encouraged to share their personal experiences using the system, provide specific feedback on features that need improvement, and discuss motivations and challenges related to maintaining effective childhood asthma management behaviors. When choosing participants, we will consider sociodemographic factors such as the child’s gender, place of residence, parental education level, and asthma severity. The interview will cover topics such as personal experiences, suggestions for improving the AI-HEALS system, reasons for maintaining self-management behaviors, and challenges faced. We will keep recruiting participants until we reach data saturation to obtain a wide range of information. All interviews will be recorded and transcribed word-for-word to ensure anonymity, and the data will be analyzed using NVivo 12 (Version 12, QRS International, Doncaster, Australia).

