Assess the extent to which a three-month intervention program grounded in the AI-HEALS improves clinical outcomes in childhood asthma patients’ physiological indicators.Evaluate how effectively the three-month comprehensive intervention program can improve the psychological indicators of the parents of children with asthma.Ascertain the effectiveness of the three-month comprehensive intervention program in promoting self-management behaviors among the parents of children with asthma.

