### Recruitment

2.5

This study endeavors to recruit families of children with asthma who satisfy the inclusion and exclusion criteria at the target hospital. The recruitment process will be spearheaded by the hospital’s medical team. They will identify and extend invitations to eligible patients when they are admitted to the hospital. Subsequently, the research team will carry out an initial face-to-face communication with the patients. During this communication, detailed information about the study’s objectives, procedures, potential benefits, and possible risks will be provided. Eligible patients will be invited to the hospital for a thorough health assessment. This assessment includes a detailed review of the child’s asthma history and symptoms. After making certain that the patients have a full understanding of the study and answering any questions they might have, the families of children with asthma will be requested to sign an informed consent form. Only those who sign the informed consent form will be formally enrolled in the study.

Participants will receive a three-month AI-HEALS intervention. Additionally, this study employs fixed measurement agents to ensure reliability of self-report measures. Specifically, the same family member who initially accompanied the child to the first hospital visit will be designated to complete all self-report assessments throughout the study period to maintain measurement consistency. To encourage maximum participation, as an incentive for their involvement, all participants will receive a free medical consultation after the study.

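### The parental mixed model adjusts for five background factors but not for the baseline score of the scale being analysed, although Table 1 collects it; adding it is a free gain in precision

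*Protocol article*

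**What the plan says.** The second study aim, at the end of the Introduction, is to "Evaluate how effectively the three-month comprehensive intervention program can improve the psychological indicators of the parents of children with asthma". Section 2.12 gives the model for parental outcomes: "For parental outcomes (continuous data), a two-level linear mixed model was applied to evaluate intervention effects, adjusting for family-level variables (marital status, household income"), and then, at parent level, age, education and parenting styles. For its random part, "we employed multilevel models with family-level random intercepts to account for within-family correlations". For the reported effect, "comparisons of estimated marginal means were conducted using the emmeans package to test between-group differences". The section names no time term, arm-by-time term, change score or common-baseline constraint for this model.

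Section 2.10 states "Physical examinations and questionnaires are scheduled to be completed at the baseline, upon discharge, and at the end of the intervention". Table 1 is more specific. PHQ-4, PSSS-SF and NGSES-SF are ticked at baseline, discharge and 3 months; EQ-5D-5L and B-PSQI are ticked at baseline and 3 months only. Section 2.9.2 places EQ-5D-5L and the short sleep index under parental behaviour. The psychological outcomes are self-efficacy, mood and social support. Section 2.5 fixes one family member per child, who "will be designated to complete all self-report assessments throughout the study period to maintain measurement consistency".

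**The concern.** A parent's score at entry is usually the strongest single predictor of the same parent's score three months later. The model spends its degrees of freedom on marital status, income, age, education and parenting style and leaves that predictor out, although it is already collected. With about 25 families per arm, two things follow. The between-arm difference carries variance that the data could remove, and part of any chance difference between arms at entry stays in the 3-month result. This affects the second study aim and the parental behaviour scales that go through the same model.

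**Working it through.** **Inputs from the protocol article.** 25 analysed per arm (section 2.4), 1:1 allocation (section 2.2), two-sided 5% level (section 2.12), measurement times (Table 1). The plan's total of 60 is 50 × 1.20 = 60 and is not in dispute here. With 20% attrition, 60 × 0.80 = 48 remain, or 24 per arm, which barely changes what follows.

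**Assumption.** The plan gives no correlation (rho) between baseline and 3-month scores, so 0.3, 0.5 and 0.7 are used. Results are in units of the score's SD, taken as equal across visits and arms.

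**Step 1: 3-month difference without baseline.** SE = √(2/25) = 0.283 SD. The 95% half-width is 2.011 × 0.283 = 0.57 SD (t on 48 degrees of freedom).

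**Step 2: with the baseline score as covariate.** The SE is multiplied by √(1 − rho²). Estimating the slope in a small sample adds a factor √(1 + 1/(2n − 4)) = √(1 + 1/46) = 1.011. The t value on 47 degrees of freedom is 2.012.

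| rho | √(1 − rho²) | SE reduction | 95% half-width, with the 1.011 factor |
|---|---|---|---|
| 0.3 | 0.954 | about 5% | 2.012 × 0.283 × 0.954 × 1.011 = 0.55 SD |
| 0.5 | 0.866 | about 13% | 2.012 × 0.283 × 0.866 × 1.011 = 0.50 SD |
| 0.7 | 0.714 | about 29% | 2.012 × 0.283 × 0.714 × 1.011 = 0.41 SD |

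The SE reductions are before the 1.011 factor, which takes back about one percentage point. In 20,000 simulated trials at rho = 0.5, the adjusted SE was 0.872 of √(2/25), against 0.866 × 1.011 = 0.875 expected.

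**Step 3: chance imbalance.** The baseline difference between arms has an SD of 0.283. The probability that it exceeds 0.3 SD in either direction is 2 × (1 − Φ(0.3/0.283)) = 29%. The expected shift in an unadjusted 3-month difference is rho × imbalance. For a 0.3 SD imbalance this is 0.09, 0.15 and 0.21 SD at rho = 0.3, 0.5 and 0.7. Among simulated trials at rho = 0.5 with a baseline difference near 0.3, the unadjusted 3-month difference averaged 0.147 and the adjusted one about 0.

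**Step 4: baseline as an outcome row.** With one respondent per family, a family random intercept can be estimated only from repeated measurements. For EQ-5D-5L and B-PSQI this would require the baseline value to be a response, so this reading has to be considered.

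- *Arm-by-time, no constraint on baseline means.* With complete data, the 3-month marginal-mean difference equals the raw 3-month difference. In 200 simulated fits the largest discrepancy was 9 × 10⁻¹⁶. It is not baseline-adjusted.
- *Change contrast from that model.* The SE factor is √(2(1 − rho)) = 1.18, 1.00 and 0.77 at rho = 0.3, 0.5 and 0.7, each larger than in the table. An imbalance now shifts the estimate by −(1 − rho) times its size.
- *One group contrast pooled over time.* No effect can exist at baseline, so with two time points a true effect d is estimated as (0 + d)/2 = d/2. With three equally weighted time points it is (0 + discharge effect + 3-month effect)/3.
- *Arms constrained to a common baseline mean.* This removes the problem, but no such model is described.

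**The case against.** The strongest reply is that a condensed article need not list every model term and that a fuller plan may add baseline. The Discussion mentions clinical as well as demographic covariates, and the parental list contains no clinical one, so the list may not be exhaustive. This carries some weight. But section 2.12 goes beyond a sketch: it sorts the covariates by level and names the contrast and the package. A general remark in the Discussion does not supply the baseline score.

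A second reply is that a mixed model with one respondent per family implies repeated measurements, so baseline may be a response and would not appear as a covariate. That is a fair reading, but step 4 shows that it does not restore the adjustment unless the baseline means are constrained.

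Four stronger conclusions are tempting and are not supported:

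- *The parental estimates are biased.* Under randomisation the unadjusted 3-month difference is unbiased on average.
- *The effect will be halved.* That requires pooling baseline and 3 months into one group contrast, which section 2.12 neither states nor excludes. It would apply only to scales with two time points. Of the parental scales considered here, these are EQ-5D-5L and B-PSQI, which section 2.9.2 does not count as psychological outcomes.
- *Baseline imbalance passes in full into the result.* Only rho times the imbalance does.
- *The pilot's variability estimates suffer.* SDs are reported descriptively, and the correlation can be computed from the collected data whatever the covariates are.

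Section 2.4 also says the trial was not designed for hypothesis testing. This weakens any argument from power, so the case here rests on interval width, which matters equally for estimation. Baseline is taken around a hospital admission, so a low correlation is plausible and the gain may lie at the small end.

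**Conclusion.** The point holds as a matter of efficiency. The stated parental model leaves out a baseline score that Table 1 collects, and none of the unconstrained readings of the text gives a baseline-adjusted 3-month difference. The size depends on the assumed correlation: the gain is slight at 0.3, worth having at 0.5 and large at 0.7. A time-pooled contrast would dilute the effect, but this is a risk left open by the wording and not something the plan prescribes. Severity is moderate: these are secondary outcomes of a pilot, and the correction is a free improvement.

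**What to change.** In section 2.12, state that each parental model includes the baseline score of the same scale as a covariate, uses only post-baseline values as outcomes, and reports the between-arm difference at 3 months. For PHQ-4, PSSS-SF and NGSES-SF, which are also measured at discharge, keep the random intercept and add time and arm-by-time terms. For EQ-5D-5L and B-PSQI, with one post-baseline value, use a baseline-adjusted linear regression without a random intercept. A mixed model that keeps baseline as a response and constrains the arms to a common baseline mean is an equivalent alternative.

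The cost is one sentence and one degree of freedom per model for the baseline score. No new data or visits are needed.
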